### Intervention

The control group will not receive ONS. The intervention group will receive preoperative nutritional support (Resource 2.5 Compact® or Nutridrink Compact®) two doses per day two weeks before the operation, and nutritional support will continue for 10 days after the operation.

Resource 2.5 Compact® was chosen as the ONS to ensure patient compliance because it is a protein- and energy-rich product with a small portion size. It does not contain fiber, which might cause abdominal discomfort. When Resource 2.5 Compact was no longer available, Nutridrink Compact was chosen as the ONS. The products are equal in size and contain the same amount of calories, proteins, carbohydrates and fat. All patients will be given written information about recommended nutrition for colon cancer patients going to and recovering from surgery. The nutritional recommendations are written by a local licensed nutritional therapist based on the literature and her clinical experience [24]. The information includes recommendations to use nutritionally rich, healthy foods in ways that they are easily digested and would not cause bloating or provoke bowel occlusions. Patients will be encouraged to eat vegetables, fruits, whole grains, milk products, fish and meat or plant-based proteins. Regular mealtimes will be emphasized, and it will also be highlighted not to seek to lose weight during cancer treatment. The demand for protein may be elevated (1.5 g/kg/day) during the treatment phase, and examples of how to obtain enough protein from the diet will be given to the patients.

Thus, the randomization groups will be:no oral nutritional support (control group) *n* = 159pre- and postoperative oral nutritional support (intervention group) *n* = 159

### Nutritional status assessment

In this study we will use several methods to analyze patients’ nutritional status. The NRS-2002 is a screening tool designed to assess the risk of malnutrition, as shown in Table 1 [25]. It takes into account BMI, weight loss during the past three months, food consumption during the past week, the severity of the illness and age under/over 70. Maximum points are 7. Patients who scored 0 are not at a nutritional risk, patients who scored 1–2 are at a low nutritional risk, and patients who scored 3–4 are at a moderate risk of malnutrition. A score of 5 or more indicates a severe risk of malnutrition. In our study, each patient will be scored a minimum 2 points at baseline and at the one-month follow-up visit because of their disease severities since these patients have local cancer and an upcoming or recent major abdominal operation.

**Table 1 Tab1:** NRS-2002 screening tool

1. Nutritional situation			Points
	BMI	< 18.5	3
		18.5–20.5	2
		> 20.5	0
	Weight loss during last 3 months	weight loss < 5%	0
		weight loss 5–10%	1
		weight loss 10.1–15% (or > 5%/2 months)	2
		weight loss > 15% (or > 5%/1 month)	3
	Food amount last week	ate normal amount	0
		ate over 50% of normal	1
		ate approximately 50% or less of normal	2
		ate very sparingly	3
			max points 3
2. Severity of disease nutritionally		normal situation (no significant disorders)	0
		Mild • patient on his/her feet despite of deteriorated overall condition • chronically sick patient staying in hospital due to comorbidities • chronic wound below 25 cm^2^ • local cancer • alcohol or drug problem	1
		moderate • bedridden patient • ambulatory patient with, e.g., widespread cancer, severe inflammatory bowel disease, recent major abdominal operation, repeated operations, recent stroke, severe infection, burn injury, pressure ulcer, widespread chronic wound, hip fracture, multiple traumas, acute leukemia	2
		severe • intensive care • head injuries • stem cell transplantation • anorexia nervosa	3
3. Influence of age	Age	< 70	0
		≥ 70	1

*Abbreviations*: *BMI* Body Mass Index

Bioimpedance analysis has been shown to be reliable in analyzing the nutritional status and body composition of a patient with a cancer [26, 27]. It measures body tissue resistance and reactance, giving an estimate of total body water. When the patient’s height is known, the estimation of fat-free mass can be calculated [28, 29].

A reliable estimation of physical strength can be measured by the handgrip strength. It has also been proven to be a method for screening malnutrition, and it was also shown that patients who were at risk of malnutrition according to NRS-2002 had a lower handgrip strength [30, 31]. A low handgrip strength has been associated with increased mortality [32].

Laboratory markers have been considered an easy method for assessing malnutrition. Traditionally, the laboratory parameters albumin, CRP and total lymphocyte count have been used [33].

Computed tomography (CT) can be used to assess body composition and lean body mass. Lean body mass is described as the sum of fat-free mass. The cross-sectional area of muscle and fat at the level of L3 has been shown to correlate with the volume of tissues in the whole body [34]. Sarcopenia and myosteatosis can be calculated with a CT scan. Sarcopenia is defined as a skeletal muscle index (SMI) < 41cm^2^/m^2^ for women, 43cm^2^/m^2^ for men with BMI < 25 kg/m^2^ and 53 cm^2^/m^2^ for men with BMI ≥ 25 kg/m^2^ [35]. Myosteatosis is defined as a Hounsfield unit (HU) < 41 for patients with BMI < 25 kg/m^2^ and HU < 33 for patients with BMI ≥ 25 kg/m^2^ [35].

### Surgery

Standard treatment of colon adenocarcinoma includes either a left or right hemicolectomy depending on the location of the tumor. Most operations for colon cancer are accomplished by laparoscopic techniques with the exception of T4 tumors and tumors of the transverse colon, of which a laparotomy is used. If the lymph node status is positive, or there are any other signs of a high risk of recurrence, a patient is considered for adjuvant therapy by an oncologist.

Perioperative care includes the assessment and optimization of medical risk factors, thromboprophylaxis with low-molecular weight heparin and elastic compression stockings, standard anesthesia with epidural analgesia, avoidance of hypothermia and increased oxygen concentrations. Mechanical bowel preparation will be performed according to local hospital policies. In perioperative care the Enhanced Recovery after Surgery (ERAS) protocol will be followed.

### Data collection

All data will be collected prospectively using an electronic database designed for this study. The reasons for withdrawal, if any, will be documented. All data will be handled confidentially and pseudonymously.

For each participant, data collection will proceed as follows. The height and weight will be measured. BMI will be calculated. At baseline, the body weights three and six months previously will be obtained from the patients. The American Society of Anesthesiologists (ASA), WHO classification and Charlson Comorbidity Index will be recorded. History of smoking, comorbidities, additional supplement use and the patient’s medication will be recorded. The patient’s symptoms, date of first symptoms and date of diagnosis will be recorded. Whole-body computed tomography will be performed to assess the possibility of metastases or locally spread cancer and also to measure body composition. Colonoscopy findings will also be recorded.

The NRS-2002 score will be calculated on each time point. Each patient will score 2 points for disease severity at randomization and at the one-month follow-up visit because they have local cancer and upcoming or recent major abdominal operation. Bioimpedance analysis will be performed (Tanita 980) and the handgrip strength will be measured. Patients will keep a food diary (Supplementary file 1) for four days before the surgery and for four days at both one- and three- month time points after the operation to assess the energy and nutrient consumption. The actual consumption of the ONS will be recorded in both groups before and after the surgery.

Laboratory parameters including leukocytes, hemoglobin, C-reactive protein (CRP), carcinoembryonic antigen (CEA), creatinine and albumin concentrations will be measured. Cytokine levels will be examined. Samples of plasma, serum and whole blood will be saved at -80 °C for later analyses.

The surgical specimen will all be analyzed by a pathologist, and study pathologists will review the cancer type, grade and classification of malignant tumors (pTNMs) according to TNM8. In addition, the degree of inflammatory reaction at the tumor margin will be recorded using the Klintrup-Mäkinen score [36], and the number of lymphoid structures will be measured according to Väyrynen et al.’s method [37]. The number of intraepithelial lymphocytes and the SMI status will be recorded. The amount of tissue necrosis will be recorded [37]. Samples of subcutaneous and visceral fat tissue, rectus abdominis muscle, liver, tumor, healthy-looking bowel wall (including all layers), peritumoral bowel wall and stool samples will be collected during the operation. Samples will be taken for histological and biochemical analyses. In right-sided cancers, a sample from the terminal ileum will also be taken. The sample´s warm and cold ischemia times will be recorded.

A RAND-36 quality of life questionnaire and an exercise questionnaire (Supplementary file 2) will be completed at every time point [38].

Data about preoperative blood transfusions, oral iron use or intravenous iron infusions will be collected. Operation data will also be collected: operation code, duration, blood loss, infused units of red cells, infused amounts of crystalloids and colloids, bowel preparation before the operation, peroral and intravenous antibiotic use, vasopressor use during the operation, operating surgeon, anastomosis technique, stoma use, operation type and intraoperative complications.

Complications after the primary operation will be collected. Data concerning the length of stay in intensive care and total length of stay in hospital and discharge to home or institution will be collected. The date of first flatus, first passage of stool, use of ONS during hospital stay and ambulatory capacity during hospital discharge will be collected.

Complication data after the primary operation and after possible reoperations will be collected at every follow-up time point. The comprehensive complication index (CCI) will be analyzed. Registered complications include wound, respiratory, cardiovascular, gastrointestinal, anastomosis leakage, urogenital and renal, thromboembolic complications and other infections. The Clavien-Dindo classification will be determined for every complication.

The side effects of chemotherapy will be monitored, as well as discontinuation of chemotherapy. Information about cancer recurrence will be collected at every follow-up point.

### Follow-up

The follow-up protocol is presented in Table 2.

**Table 2 Tab2:** Schedule of events

Schedule of events	1st meeting	Operation	Discharge	30 day	3 month phone call	1 year	2 year	5 year
Informed consent	x							
NRS-2002	x			x		x	x	x
Laboratory tests	x			x	x	x	x	x
Stool sample	x	x				x	x	x
CT scan	x					x		
BMI	x	x		x		x	x	x
Hand grip strength	x	x		x		x	x	x
Bioimpedance	x			x		x	x	x
Food diary	x			x	x			
QoL	x			x	x	x	x	x
Colonoscopy	x						x	x
Exercise questionnaire	x			x	x	x	x	x
Protocol deviation^a^	x^a^	x^a^	x^a^	x^a^	x^a^	x^a^	x^a^	x^a^
Complications and cancer recurrence		x^a^	x^a^	x^a^	x^a^	x^a^	x^a^	x^a^
Study exit form								x^b^

*Abbreviations*: *NRS-2002* Nutritional risk screening 2002, *CT* Computed Tomography, *BMI* Body Mass Index, *QoL* Quality Of Life

^a^ Complete if applicable

^b^ Complete when lost to follow-up, consent withdrawal, or when the subject has completed all study-related visits

#### First meeting and the operation

All patients attending this study will visit the outpatient clinic two to three weeks prior to the surgery. In the first meeting, patients are randomized by NRS-2002 as described. Bioimpedance and handgrip strength are measured. Laboratory tests, colonoscopy and CT scan results are registered. Patients will fill out a QoL questionnaire [38] and an exercise questionnaire (Supplementary file 2). Salivary samples are taken. A food diary (Supplementary file 1) is given to patients, and patients will return it when they present for their operation. The food diary will be checked upon return by a clinical nutritionist. All patients are given cancer patient nutrition guidelines. On arrival at the operation, BMI and handgrip strength will be measured. Data on patients’ ONS intake will be collected.

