### Trial design

The Peri-Nutri trial is a prospective, multicenter, nonblinded, randomized study. Consecutive patients diagnosed with primary colon adenocarcinoma and considered for radical surgical procedures are enrolled in this study. The trial was approved by the Ethics Committee at Oulu University Hospital and registered at Clinical Trials NCT03863236. Patient recruitment started in April 2019 at the Oulu University Hospital, November 2019 at the Seinäjoki Central Hospital and in April 2021 at the Kuopio University Hospital. Recruitment will be completed on approximately April 1, 2023. The study flow is illustrated in Fig. 1. The design of this study is open label. Blinding is not possible because there is no adequate ONS-placebo product to use. Blinding is not possible for surgeons because they recruit the patients, participate in patient care and collect the data.

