### Randomization and allocation

Patients undergoing surgery for primary adenocarcinoma of the colon and fulfilling the inclusion criteria will be randomized on their preoperative visit to the outpatient clinic approximately two to three weeks prior to surgery after signing an informed consent form. The patients will be randomly allocated (1:1 ratio) to either an intervention group or a control group according to a computer-generated list compiled by a biostatistician otherwise uninvolved in the clinical care of the trial patients. Allocation will be stratified according to NRS-2002 results (2, 3–4 and 5) and blocked within strata using random permuted blocks (block sizes 2, 4, 6 and 8). A separate randomization list will be created for each participating center. All patients undergoing surgery for colon cancer will be approached and assessed for eligibility and, once their consent is obtained, randomization will be performed. The random allocation will be performed in Case Report Forms (eCRF) where the treatment group cannot be seen before both patient consent and all eligibility criteria fulfilled.

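### The release rule lets the open-label arm be known before baseline RAND-36 and grip strength are taken, which may bias secondary comparisons that use those baselines

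*Protocol article*

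**What the plan says.** All references are to the protocol article.

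- **Eligibility criteria.** The inclusion and exclusion criteria are verified first. The patient is then informed about the study and consent is taken.
- **Randomization and allocation.** Patients "will be randomized on their preoperative visit to the outpatient clinic approximately two to three weeks prior to surgery after signing an informed consent form". This section adds that "once their consent is obtained, randomization will be performed", and that in the eCRF "the treatment group cannot be seen before both patient consent and all eligibility criteria fulfilled". These are the only two release conditions given.
- **First meeting and the operation.** "In the first meeting, patients are randomized by NRS-2002 as described. Bioimpedance and handgrip strength are measured". Registration of laboratory, colonoscopy and CT results follows, then the RAND-36 and exercise questionnaires.
- **Table 2.** RAND-36 is scheduled at the first meeting, 30 days, 3 months, and 1, 2 and 5 years. Grip strength is scheduled at the first meeting, the operation, 30 days, and 1, 2 and 5 years. No order within the first meeting is given.
- **Trial design.** "The design of this study is open label". On the staff: "Blinding is not possible for surgeons because they recruit the patients, participate in patient care and collect the data".
- **Secondary outcomes and Secondary objectives.** Quality of life after surgery is a listed secondary outcome. Better nutritional status is a secondary aim.
- **Statistical analysis.** Adjustment is for NRS-2002 stratum. Continuous outcomes are compared by mean differences, and random effect models are used when there are more than two repeated measurements. The role of baseline values is not stated.

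**The concern.** RAND-36 is self-reported and grip strength depends on effort. Either can shift when the patient, or the person taking the measurement, knows the arm. A patient just told that there will be no supplement may report lower well-being, and one told that there will be a supplement may report higher. A reading taken after that news is a post-randomisation variable, although the analysis would treat it as a baseline.

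Table 2 schedules only one RAND-36 before surgery. If it is taken after allocation, no clean baseline exists, and no later analysis plan can create one. For grip strength, the next reading is at the operation, after the preoperative supplement period.

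**Working it through.** **Step 1. Can the arm be released before the baselines are taken?**

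| Point | Section | What follows |
|---|---|---|
| Criteria verified, then consent | Eligibility criteria | Both release conditions can be met at signature |
| Randomisation follows consent | Randomization and allocation | No further step is required in between |
| Arm hidden until consent and eligibility | Randomization and allocation | Baseline completion is not a condition |
| RAND-36, exercise, grip strength and bioimpedance absent from the criteria | Inclusion and exclusion criteria | The eligibility condition does not secure them |
| Randomisation named first | First meeting and the operation | Consistent with early release, but no before or after is stated |

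The stated rule therefore permits release first. It does not direct it.

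**Step 2. When would a shifted baseline reach a treatment comparison?**

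Let d be the between-arm shift in reported baseline caused by knowing the arm (supplement minus control).

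- Follow-up values only: bias = 0.
- Change from baseline: bias = −d.
- Baseline as covariate with slope b: bias = −b × d.
- Baseline as a time point in a random effect model: a contrast of change behaves like the change score. A contrast at a later visit need not be affected.

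With d positive, as in the scenario above, change-score and covariate analyses understate any benefit of the supplement.

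**Step 3. Illustration in points.** The documents give no value for d or b. Assume d = 2 to 5 on the 0–100 RAND-36 scale and b = 0.4 to 0.6.

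- Change score: 2 to 5 points.
- Covariate: from 0.4 × 2 = 0.8 to 0.6 × 5 = 3.0 points.

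**Step 4. Illustration as type I error.** First the plan's own sample size, since it supplies n. For 36.9% against 22.0%, two-sided 5% and 80% power, with unpooled variance:

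n = (1.960 + 0.842)² × (0.369 × 0.631 + 0.220 × 0.780) / 0.149² = 142.98, so 143 per group. Then 143 / 0.9 = 158.9, so 159. Both match the article, and this point does not change them.

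Now take 143 per arm, no true effect, a baseline shift of 0.1 to 0.3 SD and a baseline/follow-up correlation ρ of 0.3 to 0.7 (all but n assumed). In SD units the standard error is √(2/143) times 1 for follow-up only, √(2(1−ρ)) for change, and √(1−ρ²) for baseline-adjusted. The adjusted bias is ρ × shift. Type I error is Φ(bias/SE − 1.96) + Φ(−bias/SE − 1.96).

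| Shift (SD) | ρ | Follow-up only | Change score | Baseline-adjusted |
|---|---|---|---|---|
| 0.1 | 0.3 | 5.0% | 11.0% | 5.8% |
| 0.2 | 0.5 | 5.0% | 39.4% | 16.4% |
| 0.3 | 0.7 | 5.0% | 90.6% | 70.1% |

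These are two-sided rejection rates. In the scenario above the excess rejections point against the supplement.

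**The case against.** **The first-meeting text is a list, not a sequence.** "Laboratory tests, colonoscopy and CT scan results are registered" also comes after the randomisation sentence, yet low serum albumin and metastatic disease are exclusions that must be known before allocation. Consent is not mentioned in that paragraph at all. This stands in part. A reader might infer that the arm is in fact released before the baselines, and the article does not say so. But registering results can mean entering values already in hand, whereas measuring grip strength and filling in questionnaires happen at the visit. The two-condition release rule carries the point without relying on sentence order.

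**Order within a visit is detail for the full protocol or site procedures.** That would be fair if the article were silent. It is not: it states when randomisation occurs and what unlocks the arm, and the rule as stated leaves the baselines unprotected.

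**The route to bias is not in the document.** A reader might infer that bias must pass into the secondary comparisons. The text does not support this. The statistical section names only the NRS-2002 stratum for adjustment, and the outcome is quality of life after surgery, not change. Use of baseline is nonetheless plausible, because RAND-36 is completed at every time point and the random effect models could include the first meeting.

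**Scope.** Exercise is not a named outcome. Grip strength is one of several measures bearing on the nutritional-status aim. Unblinded reporting also affects every follow-up questionnaire, which the article accepts as unavoidable. All of this stands. The baseline reading, unlike the later ones, can be protected at almost no cost.

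**Conclusion.** The point holds as a gap in a stated rule, not as a demonstrated bias. The allocation can be released as soon as consent and eligibility are complete, so the only pre-operative RAND-36 and the first grip-strength reading can be taken with the arm known.

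Harm needs three things together: the baselines are taken after release, knowledge of the arm shifts them, and the analysis uses them. The article settles none of the three. If all hold, the illustrated error is 2 to 5 RAND-36 points for change scores and 0.8 to 3.0 points after baseline adjustment, against the supplement in the scenario considered. The shifts and slopes behind those figures are assumptions.

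A reader should not infer a threat to the main result or a false claim of superiority. Thirty-day complications have no baseline value, and the sample size is untouched.

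**What to change.** 1. In the sections on randomization and on the first meeting, state that RAND-36, the exercise questionnaire, grip strength and bioimpedance are completed before randomisation.
2. Add completion of these forms to the eCRF as a third condition for showing the treatment group.
3. For patients already randomised, report whether baseline was taken before or after allocation, where times are available. Where it was after or is unknown, give a follow-up-only comparison as a sensitivity analysis for quality of life and grip strength.

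Do not exclude patients on this ground. No section says that the timing is recorded, and exclusion could remove nearly everyone.

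**Cost.** No new visit or measurement is needed: the same meeting runs in a set order, with one eCRF check. The patient learns the arm somewhat later in the visit. A change during recruitment mixes two procedures over time, but allocation is 1:1 in permuted blocks within each centre, so both arms meet the change alike. If sites already work in this order, one clarifying sentence and the eCRF check close the matter.

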#### Postoperative care

Postoperative care follows the ERAS protocol. Operative and postoperative data are registered as described in data collection.

